### Parenting for Lifelong Health-Teens

Parenting for Lifelong Health (PLH) for Adolescents (PLH-Teens, known in Tanzania as Furaha Teens or “Happy Teens”) is among few low-cost parenting interventions for families with adolescents that have been rigorously tested in LMICs [37]. Originally developed and tested in South Africa, PLH-Teens is a parenting program rooted in social learning theory and behavior change principles that aims to reduce adolescent exposure to violence in the home and community by improving positive parenting and parent-child communication, while reducing familial conflict, harsh discipline, parenting stress, adolescent conduct problems, risky behavior, and mental ill health [38, 39]. Trained school and community facilitators engage parents/caregivers and adolescents in 14 weekly group sessions of approximately three hours in length using non-didactic, participatory methods including discussions, role-plays, problem-solving, and experiential activities [39]. As part of their participation, families receive incentives including meals and school supplies. Facilitators also assist families in developing child safety plans, responding to abuse, budgeting, and accessing medical and social services. Thus, PLH-Teens tackles a multitude of upstream and downstream contextual factors that lead to increased risk of VAC (e.g., [40–43]).

A recent cluster randomized trial in South Africa (*N* = 40 clusters, 552 parent/caregiver-adolescent dyads) found intervention effects for reduced abuse and corporal punishment as well as improved positive parenting, involvement, and monitoring based on caregiver reports at 5 to 9 months’ follow-up [37]. Effects on secondary outcomes included reductions in both adult and child substance use and parental stress, depression, endorsement of corporal punishment, and financial stress [37]. A cost-effectiveness analysis of PLH-Teens found that the intervention cost $972 USD per case of abuse prevented [44].

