### PLH-Teens in Tanzania

Encouraging results from the cluster RCT [37] have contributed to the rapid dissemination of PLH-Teens in 16 countries to approximately 300,000 beneficiaries. Among these is the large-scale implementation of PLH-Teens in Tanzania that started in 2017 as part of the Kizazi Kipya (or “New Generation”) Project by Pact Tanzania. Kizazi Kipya is a USAID-PEPFAR-funded project aiming to enable more Tanzanian orphans and vulnerable children (OVC)—children, adolescents, and young people orphaned and made vulnerable by HIV and other adversities—to use age-appropriate HIV- and AIDS-related and other services for improved care, health, nutrition, education, protection, livelihoods, and psychosocial well-being. Through Kizazi Kipya, Pact Tanzania implements the DREAMS Initiative (Determined, Resilient, Empowered, AIDS-free, Mentored, and Safe) which aims to reduce HIV infection among adolescent girls and young women in HIV priority areas. As part of DREAMS, Pact is implementing the locally adapted and HIV-enhanced version of PLH-Teens, known as the Furaha Caring Families Program for Parents and Teens (Furaha Teens), for adolescent girls aged 9–14 and their parents/caregivers.

In 2020–2021, Pact is scaling-up PLH-Teens with 444 trained facilitators and 70 coaches to reach an additional 100,000 beneficiaries (approximately *N* = 50,000 adolescents and *N* = 50,000 parents/caregivers). The 2020–2021 delivery of PLH-Teens in Tanzania offers an unprecedented opportunity to examine the intervention and implementation outcomes when delivered at scale. As a result, this study—the Furaha Adolescent Implementation Research or FAIR study—will provide vital information on how to establish, implement, improve, and sustain high-quality delivery of PLH-Teens. The findings will also be of value to other parenting programs aiming to prevent VAC at scale.

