### Study aims and research questions

The FAIR study aims to examine the quality of implementation of PLH-Teens and its impact on preventing and reducing VAC at scale in Tanzania as well as consider factors associated with implementation and how implementation can be improved to optimize intervention impact. The study seeks to answer the following research questions: (1) what is the level of program implementation of PLH-Teens in terms of quality of delivery and implementation fidelity; (2) what factors are associated with the quality of delivery and implementation fidelity of PLH-Teens; (3) how are implementation quality and fidelity associated with intervention outcomes; (4) what are participant and implementing staff perspectives on the acceptability, appropriateness, feasibility, benefits, and challenges of delivering PLH-Teens in their schools and communities; (5) what is the impact of PLH-Teens on VAC and family well-being; and (6) how much does it cost to deliver PLH-Teens at scale?

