## Methods

This mixed-methods study involves the integration of quantitative and qualitative methods to address the research questions. The data sources to be used are outlined in Table 1. Qualitative (including focus group discussions, in-depth interviews, and observation) and quantitative (merged secondary data collected via routine monitoring and evaluation by Pact Tanzania, local implementing partners or LIPs, and Clowns Without Borders South Africa or CWBSA) methods will be used to explore the impact, acceptability, appropriateness, feasibility, fidelity, and cost of PLH-Teens. As randomization to intervention and control groups is not possible, the study will make the most of the routine service delivery data available. Analyzing this data will allow for a unique inquiry into the real-world implementation of a parenting program at scale.

**Table 1 Tab1:** Matrix of data collection methods

Type of data	Data collectors	Data collection method	Study participants
Primary data	FAIR research team	Focus group discussions	Adolescents
			Parents/caregivers
			Furaha facilitators and coaches
		In-depth interviews	Program coordinators and directors
			Pact Monitoring and Evaluation (M&E) team
			Furaha facilitators and coaches
			School principals
		Structured observations	Furaha Teens group sessions
			Furaha Teens coaching sessions
		Community of practice meeting	LIP and Pact staff
		Document review	All of the above
Secondary data	Pact Tanzania and LIPs (collected by Furaha facilitators) and other team members	Family reports of parenting practices, child behavior, child and caregiver mental health (routine data)	Parents/caregivers and adolescents
		Family enrolment, attendance, engagement, and dropout	
		Cost data	Facilitators, coaches, and LIP staff
		Surveys on the sociodemographic and professional background of facilitators and coaches delivering the program	Furaha facilitators and coaches
	CWBSA	Assessments of facilitator competent adherence	Furaha facilitators and coaches
		Assessments of coach delivery of facilitator supervision sessions	

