#### Family outcome and demographic measures

Pact Tanzania was provided with a set of process and outcome tools by CWBSA as part of the monitoring and evaluation technical support they provide to all implementing partners delivering PLH programs. CWBSA recommends and provides these tools because they are open-access and have been psychometrically tested in previous studies. Due to the large number of beneficiaries Pact Tanzania is reaching and their limited capacity to collect evaluation data, they are using abbreviated versions of the tools provided by CWBSA. An overview of these tools and their items is summarized in Additional file 8.

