A variety of data sources will be used to examine how implementation is associated with changes in VAC and family well-being. In particular, correlation and regression analyses will be used to look at whether pre-post changes in family outcomes are associated with family attendance, facilitator and coach competent adherence, and facilitator and coach characteristics, as well as LIP characteristics. Interviews, FGDs, and session observations will be used to expand upon and contextualize the findings.

#### Research question 4

Participant and implementing staff perspectives on the acceptability, appropriateness, feasibility, benefits, and challenges of delivering PLH-Teens in their communities will be examined by analyzing the interviews, FGDs, and session observations with school principals, facilitators, coaches, LIP staff, CWBSA staff, adolescents, and parents/caregivers.

#### Research question 5

Changes in VAC and participant well-being will be analyzed based on data gathered from parent/caregiver pre-post questionnaires, adolescent pre-post questionnaires, interviews, and FGDs. Multi-level models will be used to examine differences in pre- to post-intervention family-level outcomes and to compare differences in outcomes reported by both adolescents and parents/caregivers. Variation in the pre-post changes will be examined by participant baseline characteristics, and, if possible, by parenting group and LIP. The analyses will be similar to treatment-on-the-treated analyses since all participants included in the monitoring data would have engaged with the program to some extent. The levels of change reported by participants will be compared to the levels of change reported by the treatment and control groups in the randomized trial of the program in South Africa. Where possible, the reliability of the family survey items will also be examined using coefficients such as Cronbach Alphas or Omegas.

The findings from the interviews and FGDs  will also be analyzed to explore participant perspectives on the impacts of the program on them and their families. The interviews and FGDs will also reveal what impact implementing volunteers and staff assess the program had and will have on themselves, participants, schools, and communities.

#### Research question 6

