RQ4: What are participant and implementing staff perspectives on the acceptability, appropriateness, feasibility, benefits, and challenges of delivering PLH-Teens in their schools and communities?	1) Interviews with school principals, facilitators, coordinators, coaches, and LIP staff 2) FGDs with adolescents, parents/caregivers, facilitators, and coaches 3) Direct observation of group sessions using the structured observation guide
RQ5: What is the impact of PLH-Teens on VAC and participant well-being?	1) Parent/caregiver- and adolescent-report on pre-post questionnaires 2) Individual interviews with school principals, facilitators, coordinators, coaches, and LIP staff 3) FGDs with adolescents, parents/caregivers, facilitators, and coaches
RQ6: How much does it cost to deliver PLH-Teens at scale?	1) Facilitator cost surveys 2) Facilitator profile surveys 3) Coach cost surveys 4) LIP cost surveys

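### Research question 5 asks for the impact of PLH-Teens, but the plan estimates only uncontrolled pre-post change, with an unqualified comparison to South African trial arms as its sole benchmark

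*Protocol article*

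**What the plan says.** The aims section of the protocol article asks "what is the impact of PLH-Teens on VAC and family well-being". Table 4 repeats the question as "What is the impact of PLH-Teens on VAC and participant well-being", and the abstract carries it too.

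The Methods section is open about the design: "As randomization to intervention and control groups is not possible, the study will make the most of the routine service delivery data available". Under Research question 5, multi-level models are to examine "differences in pre- to post-intervention family-level outcomes" in participating families. The text then likens this to a treatment-on-the-treated analysis, on the ground that everyone in the monitoring data engaged with the program to some extent. The only outside reference is that the "levels of change reported by participants will be compared to the levels of change reported by the treatment and control groups" of the South African trial. No alignment or caveat accompanies that comparison.

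On the trial, the background section gives 40 clusters and 552 dyads, with effects "based on caregiver reports at 5 to 9 months" of follow-up. On the Tanzanian side, the program is a "locally adapted and HIV-enhanced version of PLH-Teens" for girls aged 9 to 14. For the outcome tools, the implementing organization has limited capacity, so "they are using abbreviated versions of the tools provided by CWBSA". Table 1 shows that facilitators collect the family reports.

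**The concern.** A causal question is paired with an estimate that is not causal. In a single-group pre-post design, anything else that moves the outcome between the two surveys is counted with the program: secular trend, recovery from COVID-19 disruption, the girls growing older, regression to the mean, and a shift in how families report. The document itself makes some drift plausible. Tanzania had committed to halving violence against children by 2022, which overlaps the 2020–2021 delivery, and delivery was held up for months by the pandemic.

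The treatment-on-the-treated remark makes this worse, because it suggests the pre-post change belongs to a recognised class of causal estimate. The South African comparison could be read the same way, as a stand-in for the missing control group.

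The stakes are practical. The findings are meant to feed guidelines and policy briefs, and recommendations for Tanzania and 24 other countries. A very precise pre-post change reported as impact would carry weight there that the design cannot support.

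**Working it through.** The protocol gives no sample-size calculation, effect size or significance level for this question, so there is no figure of its own to reproduce. The check has two parts.

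**1. The two data sources side by side**

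| Feature | Tanzanian study | South African trial | Status |
|---|---|---|---|
| Country | Tanzania | South Africa | Documented difference |
| Population | Girls aged 9–14 enrolled in the Kizazi Kipya Project | 552 caregiver–adolescent dyads; age and sex mix not given | Enrolment differs; age and sex difference not shown |
| Program | Locally adapted, HIV-enhanced | Original setting of development and testing | Documented difference |
| Timing | Pre and post surveys around 14 weekly sessions (98 days, about 3.2 months); post-survey date not given | Effects at 5 to 9 months | Apparent difference |
| Measurement | Abbreviated tools, collected by facilitators | Instrument not named | Difference not established |

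**2. How large a sample does to a small bias**

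Inputs from the document: n = 50,000 dyads; 444 facilitators; 5 observed sessions with 150 participants; 552 trial dyads in 40 clusters.

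Assumptions not in the document: pre-post correlation ρ = 0.3 to 0.5; intraclass correlation (ICC) 0.03 to 0.05; equal split of the trial, so 552/2 = 276 control dyads; a drift of 0.05 SD with no program effect.

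Cluster size m is taken at two levels:
- Parenting group: 150/5 = 30 participants, or 15 dyads.
- Facilitator: 50,000/444 = 112.6, rounded to 113 dyads.

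Formulas, in baseline SD units: DEFF = 1 + (m − 1) × ICC; SE = √[2(1 − ρ)] × √(DEFF/n); z = 0.05/SE.

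| m | ICC | DEFF | SE, ρ = 0.5 | z | SE, ρ = 0.3 | z |
|---|---|---|---|---|---|---|
| 15 | 0.03 | 1.42 | 0.0053 | 9.4 | 0.0063 | 7.9 |
| 15 | 0.05 | 1.70 | 0.0058 | 8.6 | 0.0069 | 7.2 |
| 113 | 0.03 | 4.36 | 0.0093 | 5.4 | 0.0111 | 4.5 |
| 113 | 0.05 | 6.60 | 0.0115 | 4.4 | 0.0136 | 3.7 |

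The 95% half-width (1.96 × SE) therefore runs from 0.010 to 0.027 SD. In every cell, a drift of 0.05 SD is clearly significant against zero although the program did nothing.

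For the trial control arm, m = 552/40 = 13.8 and ICC = 0.05, so DEFF = 1 + 12.8 × 0.05 = 1.64.
- ρ = 0.5: SE = √(1.64/276) = 0.077; 95% half-width 0.15 SD.
- ρ = 0.3: SE = √1.4 × 0.077 = 0.091; 95% half-width 0.18 SD.

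A 0.05 SD drift is only 0.05/0.077 = 0.65 or 0.05/0.091 = 0.55 standard errors of that arm's mean change. Even if the two studies were comparable, the benchmark could neither reveal nor remove a drift that the pre-post test would flag as significant.

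**The case against.** The protocol hides nothing. It says randomization is not possible, its analysis text speaks of changes and pre-post differences, and it never says that the comparison with the trial arms proves efficacy. It says levels will be compared, not that arms will be subtracted or tested. As descriptive context such a comparison is legitimate. This is also one of six questions in an implementation study built on routine data, and item matching and standardisation are details an article may leave to a fuller document. All of that stands, and it limits the fault to wording and interpretation. It does not rescue the word impact or the treatment-on-the-treated sentence, both of which the article states outright.

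The limitations text names recall and social desirability bias and promises sensitivity checks. Those checks concern flawed and missing data, not the absent comparator.

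A reader might infer more than the documents support:
- That the two studies used different instruments. Abbreviated tools are documented for Tanzania, but the trial's instrument is not named.
- That the trial differed in age or sex mix. That mix is not given.
- That the routine data already contain a concurrent comparator in later-enrolling families. Neither staggered starts nor recorded survey dates are stated.
- That negligible sampling error also describes the comparison with the trial. It does not: the trial arm is the imprecise side.

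**Conclusion.** The point holds as a mismatch between question and estimate. As planned, the analysis can describe change among participants; it cannot attribute that change to the program. The treatment-on-the-treated statement is wrong, because such an effect is still a contrast with what the treated families would have experienced untreated. The trial benchmark differs in country, enrolment population and program version, and apparently in follow-up, and is too coarse to correct small drift.

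The size figures are illustrative. They rest on the assumed correlations, cluster sizes, equal split and 0.05 SD drift, not on anything the protocol reports. The qualitative result does not depend on where in those ranges the truth lies.

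The stronger conclusion, that the plan uses the trial arms as a formal control group or conceals its lack of one, is not supported. Severity: should be fixed.

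**What to change.** 1. In the abstract, the aims and Table 4, restate the fifth question as the pre-post change in violence against children and well-being observed among participants. Reserve impact for a contrast with a comparator.
2. Remove or correct the treatment-on-the-treated sentence under Research question 5.
3. Label the South African comparison descriptive. As far as available trial data allow, limit it to common items, the same reporter and the nearest available follow-up, standardise by baseline SD, and carry the trial arms' own standard errors.
4. Add secular trend (including COVID-19), maturation and regression to the mean to the section on data quality and potential biases.
5. Only if survey dates are recorded and group starts prove to be staggered, add a sensitivity analysis: compare post-surveys of earlier groups with baseline surveys taken in the same period from later groups in the same district and implementing partner. State that it assumes comparable waves and inherits selective completion.

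Items 1, 2 and 4 cost only wording. Item 3 depends on access to suitable trial data, which the article does not state. Item 5 would need one further model. The main price is a weaker claim for this question.

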## Discussion

This mixed-methods implementation science study is a part of the first effort of its kind to examine the large-scale implementation of a parenting program aiming to reduce VAC in East Africa. The study’s results are important for the Parenting for Lifelong Health program and broader parenting program literature as they will provide key insights into the impact, acceptability, appropriateness, feasibility, costs, and optimization of large-scale parenting program delivery in both school and community settings. As the study will also examine factors associated with program implementation and outcomes, the results will help elucidate the potential mechanisms and processes through which program delivery and impacts can be improved in future (e.g., facilitator quality of delivery).

There are a number of practical, ethical, and operational issues that will require consideration during the study. These include safeguarding, potential implementation and funding delays, data quality concerns, staff burden issues, COVID-19-related impacts, and research uptake.

### Safeguarding

Since the study involves research with children and families who may be at risk of maltreatment and other adversities, research and implementation staff will comply with international standards concerning children’s rights to protection by following a Child Protection Protocol (see OSF page). All researchers interacting with minors will be trained on child protection and have a certificate on the protection of human research subjects. If sensitive information is to be collected, staff will be required to sign a confidentiality agreement. These expectations and procedures will be in addition to Pact and CWBSA’s existing policies and practices for child safeguarding.

### Implementation and funding delays

As program implementation is reliant on timely delivery of USAID funding to the prime implementing partner, spending/disbursement delays to LIPs could impact the study’s timeline. To accommodate potential delays, a flexible timeline has been adopted.

### Data quality and potential biases

Collecting comprehensive assessments of family-level outcomes from 100,000 beneficiaries is challenging. As a result, the study relies on existing data collection tools and processes developed and used during program implementation by Pact Tanzania’s Monitoring and Evaluation team. If timing allows, the research team will conduct random checks to verify the quality of implementation and outcome data. Among the observational facilitator and coach assessments, CWBSA will double code a random sample of program delivery videos to verify the accuracy and reliability of the assessments. As a significant amount of study data relies on self-reports, this data could be limited by recall and social desirability bias.

Where relevant, the study will take into consideration advice regarding how to manage and analyze data with FUPS characteristics (flawed, uncertain, proximate, and sparse), such as by presenting the data flow, conducting statistical sensitivity checks, and making the analyses accessible [57]. In the event of missing outcome data on individuals who are eligible but not included in the sample, sensitivity analysis will be done by replacing missing data with simulated data.

### Staff burden

To mitigate the possible overburdening of implementation staff tasked with both program delivery and data collection, the study focuses on answering research questions that respond to priority questions for implementers and draws on existing data collection tools and procedures to minimize the need for additional data collection.

### COVID-19 impacts

The delivery of PLH-Teens by Pact Tanzania was delayed for a number of months due to the COVID-19 pandemic. In response, the study approach and timeline have been adjusted. For instance, COVID-related questions were added to the primary qualitative data collection. Further, researchers are remaining flexible as the situation evolves. To illustrate, preparations will be made to conduct interviews via telephone, if necessary.

